# ***Study Protocol: Text messaging and Cardiovascular Health in Type 2 Diabetes***

## ***(TEACH Study )***

**Primary Investigator: [name] M.D & Ph.D.,**

**Department of Endocrinology and Metabolism,**

**Nanfang Hospital, Southern Medical University**

### **1. Background and aim**

Diabetes has become a major public health issue around the world. Globally, the prevalence of diabetes is about 8.8% and the number of people with diabetes is about 425 million, which will rapidly rise to 629 million by 2045(1). The prevalence of diabetes is increasing dramatically in most countries around the world(1). According to a Chinese survey, the prevalence of diabetes in adults aged over 20 years increased from 2.5% in 1994 to 11.6% in 2013, which means about 114 million adults are suffering from diabetes (2). However, a study showed that the awareness, treatment, and control of diabetes were only 30.1%, 25.8% and 39.7%, respectively(2).

In the past 20 years, the total number of deaths attributed to diabetes has doubled(3), and the estimated diabetes-related death among people aged 20-79 is about 4.0 million in 2017(1). Diabetes is not only known as a major risk factor for cardiovascular diseases (CVD) but also a major cause of mortality (4-6). It is estimated that diabetes account for 21% and 13% respectively of deaths associated with CVD and stroke worldwide, and 84% of deaths induced by diabetes and CVD happen in low-income countries (7). This phenomenon is related to the poor control of diabetes and other risk factors of CVD. Most people living with diabetes are combined with multiple cardiovascular risk factors, such as obesity, hypertension and dyslipidemia, or with a history of atherosclerotic cardiovascular disease (ASCVD) (8; 9). A survey has found that 86% of Chinese adults with diabetes have at least one uncontrolled cardiovascular risk factor, such as hemoglobin A1c (HbA1c)  $\geq$  7.0%, blood pressure (BP)  $\geq$  140/90mm Hg, or low-density lipoprotein cholesterol (LDL-C)  $\geq$  100mg/dL, while 12.7%

of diabetes are complicated with ASCVD (10).

At present, many treatments, including lifestyle intervention, anti-platelet aggregation, lipid reduction and blood pressure control, have been proved to reduce cardiovascular events in patients with diabetes and are recommended in clinical guidelines (11). However, there are gaps between evidence and practice, especially lifestyle intervention, one of the most effective treatments (12), is often difficult to adhere to in clinical practice. The main reasons leading to this dilemma are lack of awareness and poor adherence (13-15). The education of the primary health service centers and increasing patient visits may help, but it is bound to greatly increase the current medical burden and costs. Therefore, seeking an efficient and universal strategy to improve lifestyle change and compliance is essential and urgent. Text messaging can remind, encourage and stimulate patients to manage the cardiovascular risk factors for diabetes, which theoretically improve their adherence and the treatment of diabetes (16-20). However, most existing studies have relatively small sample size, short intervention time (i.e., for 3–9 months), different patterns of text messaging intervention. Importantly, these existing clinical trials of mobile messaging-based interventions conducted in population with diabetes tended to focused only on glycemic control rather than multiple CVD risk factors control. Indeed, most patients with diabetes require long-term multifactorial therapy to simultaneous reduction of multiple risk factors because of its multiple comorbid conditions (21; 22). Therefore, it needs to evaluate mobile messaging-based interventions on reduction of CVD risk factors among patients with diabetes and fill the knowledge gaps.

In this randomized controlled trial, we aimed to evaluate the effectiveness of a mobile messaging-based intervention on cardiovascular risk factors management in patients with uncontrolled type 2 diabetes.

## **2. Research Design and Methods**

### **2.1 Overall design**

This study is a parallel, randomized, multicenter clinical trial with 800 participants in 5 hospitals in China with 12-months follow-up. Eligible participants with uncontrolled type 2 diabetes will be randomly assigned to the mobile messaging-based intervention or usual care for 12 months. The primary outcome comprised the mean changes in HbA1c levels, LDL-C levels, and systolic blood pressure (SBP) levels from baseline to 12

51 months simultaneously modeled for a single overall treatment effect.

[figure not shown]

52 Figure 1. study design

## 53 2.2 Randomization and masking

54 Eligible participants were randomly assigned to either the mobile messaging-based intervention or control  
55 group in a 1:1 ratio. Randomization was stratified by study centers and performed centrally at the Research and  
56 Data Coordinating Center in Nanfang Hospital. The randomization schedules were generated using the PROC  
57 PLAN procedure in SAS statistical Software with a block size of six (Version 9.4). The research nurses,  
58 investigators, and statisticians were blinded to the treatment allocation. The clinical outcomes were also  
59 collected by blinded research doctors during the study period.

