## 2.4 Intervention.

All participants included in this study will receive usual care. Participants assigned to the mobile messaging-based intervention group will receive mobile text messaging that was regularly delivered by SMS (short messaging service) platform to remind, encourage and motivate patients to participate in the behaviors needed for improving glycaemic control and CVD risk factors management. About 500 text messages are included in this study, covering 7 aspects: general information about CVD and diabetes, healthy diet, physical activity, medical adherence, glucose monitoring, blood pressure control, smoking cessation. The content of text message is based on the recommendation from the Chinese Diabetes Society(23) and American Diabetes Association(24), a text mess bank in plain language was established and modified according to Chinese diet culture and language habits. 6 messages per week will be sent through the messaging platform during the 12-month study period. Researchers will save and check the delivery log to ensure successful delivery. At each visit, participants in the intervention group are asked to confirm or update the phone number and complete a dedicated satisfaction survey questionnaire to investigate the reading proportion and satisfaction with the text messages

| Category                                        | Content/Explanation                                                   | Example                                                                                                                                                                                                                                                                    |
|-------------------------------------------------|-----------------------------------------------------------------------|----------------------------------------------------------------------------------------------------------------------------------------------------------------------------------------------------------------------------------------------------------------------------|
| General education about CVD and diabetes | Basic information about CVD and diabetes                              | At present diabetes cannot be cured, but it can be controlled through a variety of treatment methods. It mainly includes five aspects: Diabetes self-management education and support, self-monitoring of blood glucose, healthy diet, physical activity and drug therapy. |

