## **6. Quality control**

The proposed trial will comply with China's Standard for Quality Management of Clinical Trials (GCP) and other relevant laws and regulations on clinical trials. Participants' personal information will be confidential and will not be disclosed without permission.

The standard quality control process will be carried out at each step of the study, including repeated laboratory measurements in 5-10% of random blind samples, and all data will be entered independently.

Establish a research procedure manual (MOP): we will develop a standardized process of data collection, which will include the recruitment of subjects, instructions for the use of tables, intervention programs, index measurement, specimen collection and management, etc., to guide all tabular information entry and diagnosis and treatment processes, and other aspects of the study.

Training: all researchers will receive relevant training before the start of the study, including standardized processes, recruitment processes, follow-up, intervention programs, measurement procedures, and the use of MOP. At the same time, regular retraining sessions will be conducted to ensure the quality of research.

Quality monitoring and reporting: quality control personnel will regularly review the QC data, including the timeliness of the completion of the visit, data collection, program implementation and data quality.

A steering committee (SC), chaired by [name], Nanfang Hospital, Southern Medical University, is responsible for the study. The SC is responsible for organizing and supervising the research implementation, approving the research program, including significant revisions, monitoring subject recruitment and retention,

delivering of intervention programs, data collection, quality control, and respond to questions raised by the institutional review board (IRB). The research center will play a critical role in the patient recruitment, randomization, delivery of intervention, data collection, quality control, data analysis, and the report and publication of the research results.

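### A single block size of six, printed in the protocol, would make some assignments predictable if allocations reached recruiting staff during enrolment

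*Protocol*

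**What the plan says.** Protocol section 2.2 assigns participants to either "group in a 1:1 ratio". On method it states: "Randomization was stratified by study centers and performed centrally at the Research and" (the sentence goes on to name the coordinating centre). The schedules come from PROC PLAN "with a block size of six". The same section gives the masking: research nurses, "investigators, and statisticians were blinded to the treatment allocation", and the clinical outcomes are "collected by blinded research doctors during the study period".

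Three other places bear on whether that masking can last:

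- **Section 2.4.** Only the intervention arm receives messages, six a week. Researchers keep and inspect a log of deliveries. At each visit, intervention participants alone have their telephone number checked and "complete a dedicated satisfaction survey questionnaire".
- **Section 6.** "The research center will play a critical role in the patient recruitment, randomization, delivery of intervention", and the same sentence adds data collection and further tasks.
- **Table 2 (section 2.6.2).** The first visit after randomisation is at month 1.

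The protocol does not say who is unmasked, who enrols, who holds the list, or whether these are different people.

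**The concern.** With permuted blocks, once three of the six places in a block have gone to one arm, the rest must go to the other. Anyone who knows the block size and the earlier allocations in that centre can see this coming. Central randomisation hides the list, but it cannot hide what follows from a known constant block size and known past allocations. Printing the size gives every reader of the protocol one of the two pieces of information needed.

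The other piece, the past allocations, is meant to be hidden. Yet section 2.4 creates several routes by which an arm can show itself, and section 6 places recruitment, randomisation and delivery with one body without separating them.

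What is at stake is selection at entry. The exclusion in section 2.3.2 for patients unable to keep to 12 months of follow-up is a matter of judgement, and expected adherence is close to what a messaging trial tries to change. Blinded outcome measurement does not correct selection of that kind, and adjustment for baseline values corrects only the part that those values capture.

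**Working it through.** The protocol gives no figure for predictability, so there is none to reproduce.

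**Inputs.** Block size 6 and ratio 1:1, so m = 3 per arm, with centre as the stratum (section 2.2). A "multicenter clinical trial with 800 participants in 5 hospitals in China" (section 2.1).

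**Assumptions.** Equal recruitment, 800/5 = 160 per centre. Recruitment lasting 3 to 12 months, because section 8 allows about one year for the manual, training and recruitment together.

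**Step 1: upper bound, every earlier allocation in the block known at once.**

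- Certain assignments per block: 2m/(m + 1) = 6/4 = 1.5, and 1.5/6 = 25%. That is 200 of 800 if every block is complete. With 160 per centre (26 full blocks and 4 places over), it is 5 × (26 × 1.5 + 0.1) = 195.5, about 196.
- Correct best guesses per block: m + (2^(2m)/C(2m, m) − 1)/2 = 3 + (64/20 − 1)/2 = 4.1, and 4.1/6 = 68.3%.

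Enumerating all C(6,3) = 20 sequences gives the same two results.

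**Step 2: delayed disclosure.** Over the 20 sequences, the position of a guesser who has seen the first k allocations of the block is:

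| k seen | chance that the next is certain | chance that the best guess is right |
|---|---|---|
| 0 | 0 | 0.5 |
| 1 | 0 | 0.6 |
| 2 | 0 | 0.6 |
| 3 | 0.1 | 0.7 |
| 4 | 0.4 | 0.7 |
| 5 | 1.0 | 1.0 |

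Summing over the six places in a block, with the most recent allocations unknown:

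| most recent allocations unknown | certain | best guess right |
|---|---|---|
| 0 | (0.1 + 0.4 + 1.0)/6 = 25% | 4.1/6 = 68% |
| 1 | (0.1 + 0.4)/6 = 8.3% | 3.6/6 = 60% |
| 2 | 0.1/6 = 1.7% | 3.4/6 = 57% |
| 3 | 0 | 3.2/6 = 53% |
| 5 or more | 0 | 50% |

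Simulated lists of 160 per centre, where the last block is cut short, give 8.1% and 1.6% for one and two unknown.

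**Step 3: how fast a block fills.** At 160 per centre over 3 months, a block takes 6/(160/3) × 30.4 = 3.4 days. Over 12 months it takes 6/(160/12) × 30.4 = 13.7 days. The first survey is due at month 1, so by itself it would usually reveal an arm after that block had closed. The delivery log, or participants who mention their messages, could reveal an arm within 3 to 14 days if messaging starts promptly. The protocol does not give the start day.

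**Step 4: what varying the sizes does.** In simulated lists of 160 with sizes 4, 6 and 8 drawn at random, a guesser who sees every allocation and knows the set of sizes, but not their order, is certain of 2.2% of assignments. The figure for fixed blocks of six in the same simulation is 24.5%. That guesser is still right 68.0% of the time, against 68.1% with fixed blocks. Varying the sizes removes most of the certainty and almost none of the guessing advantage.

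**The case against.** The strongest reply is that the protocol already says what matters: randomisation is central, and nurses and investigators are blinded. If that holds, knowing the block size is useless. A fixed block under those conditions is ordinary and contradicts nothing. No section says that recruiting staff send the messages or that the researchers who inspect the delivery log also enrol. The research centre in section 6 may be the coordinating institution, and a list of an institution's duties does not show that one person holds them all. A participant who knows his or her own arm does not thereby tell recruiters the order of allocations within a block. The month-1 survey comes too late to help.

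Most of this stands. A reader might infer from sections 2.4 and 6 that allocations do become known to the recruiting centre, or that concealment has failed. The document does not support either. No section says so, and section 2.2 states the opposite. Nor are 25% and 68% expected values. They are the ceiling under immediate and complete disclosure.

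What does not stand is the idea that the masking statement settles the matter. It is not reconciled with intervention-only messages, a log that researchers read, and recruitment, randomisation and delivery placed with one body. The protocol names no separation of roles that would keep allocations from those who enrol.

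**Conclusion.** The point holds conditionally, as a low-cost improvement. Section 2.2 prints one constant block size within centre, and the masking it states is left exposed by sections 2.4 and 6. If allocations reach recruiting staff during enrolment, up to 25% of assignments would be certain in advance and up to 68% could be guessed. With the last one, two or three allocations unknown, certainty drops to about 8%, 1.6% and 0%, and correct guesses to 60%, 57% and 53%. With five or more unknown there is no gain over chance.

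The percentages follow from the block structure. The timing rests on the assumed equal split between centres and on 3 to 12 months of recruitment. Nothing in the protocol shows that prediction or selection would in fact occur.

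**What to change.** For lists not yet used:

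1. Generate the centre schedules with randomly varying block sizes, for example 4, 6 and 8.
2. Take the sizes out of the site-facing protocol and hold them in a restricted randomisation file.
3. State in section 2.2 who is unmasked, and that enrolment is done by people with no access to allocations or to the delivery log. Bring sections 2.4 and 6 into line with this.

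Steps 2 and 3 are essential, because step 1 leaves the best-guess rate near 68% for someone who knows the sizes and sees every allocation. Section 2.2 describes the schedules in the past tense, so it should first be checked whether any list is already in use. If one is, step 3 can still be applied to the remaining enrolment.

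The cost is a rerun of PROC PLAN, a few changed sentences and an assignment of roles. The statistical price is a maximum within-centre imbalance of 4 (half of a block of eight) instead of 3, which is trivial with 800 participants in five hospitals.

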## 60 2.3 Study Population.

### 61 2.3.1 Inclusion criteria

62 Patients will be eligible if they are adults over 18 years old with poorly control Type 2 diabetes mellitus  
63 (defined as  $HbA1c \geq 7\%$  or if combined with clinical  $CVD \geq 7.5\%$ ) comorbid with at least one risk factor for  
64 CVD (such as  $SBP \geq 140$  mmHg and / or diastolic blood pressure (DBP)  $\geq 90$  mmHg  $\geq$  and / or  $LDL-C \geq$

100mg/dL) or clinically diagnosed ASCVD (such as acute coronary syndrome, ischemic stroke, Transient ischemic attack or peripheral artery disease). All participants had access to a smartphone to read and accept text messages. All participants would provide written informed consent at the initial trial visit.

### 2.3.2 Exclusion criteria

Exclusion criteria included serious heart failure (NYHA [New York Heart Association] class III to IV), end-stage kidney disease, current or planned pregnancy, and inability to adhere to 12-month follow-up.

### 2.3.3 Termination criteria

Termination criteria: (1) Subjects with serious complications or severe adverse events; (2) Subjects are pregnant or treated with dialysis; (3) Subjects withdrawal the informed consent form, unwillingness to compliant to the intervention or other unexpected reasons.

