### **3.2 Definition of serious adverse events**

Severe adverse events (SAE) are defined as the occurrence of any acute life-threatening event, a hospitalization for any cause other than routine delivery, prolonged or permanent disability.

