### **3.4 Assessment of severity**

The severity of adverse events is assessed as follows:

Mild: usually temporary, and not affecting daily activities;

Moderate: causing discomfort and affecting normal activities, thought tolerable and not requiring participants to take any medication.

Severe: disrupting daily activities and intolerable, requiring participants to take medication immediately.

With regard to the causal-effect relationship, medical adverse events are divided into five categories: definite, probable, possible, unlikely, and unrelated. Only “definite” and “probable” are counted as adverse events.

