#### **5.2.1 Data analysis plan**

Data was analyzed according to participants' randomization assignments, regardless of their subsequent status (intention to-treat principle). All the analyses will be conducted using SAS version 9.4 (SAS Institute Inc). Group differences in the trial outcomes will be evaluated using the general linear model for continuous variables and the chi-square test for categorical variables. Continuous variables will be presented as mean  $\pm$  standard deviation (SD) or median (interquartile range), and categorical variables will be presented as frequencies with percentages. In this study, the overall intervention effect on HbA1c, LDL-C, and SBP will be tested using a scaled marginal model, in which each outcome was scaled by its SD. Generalized estimating equations will be used to calculate the regression coefficient and outcome-specific scale variables in SAS PROC GENMOD, and the assumption of an overall intervention effect will be tested using a score test(30). Group differences for the secondary outcomes will be also evaluated with the use of the generalized estimating equations for continuous variables adjusting for baseline levels corresponding to each study outcome. In addition, the correlations of outcomes among participants within each clinic center using an exchangeable

correlation structure will be also taken into account in the analysis. Multiple imputations for missing data in the multivariable analyses will be conducted using the Markov chain Monte Carlo method.

Subgroup analyses of HbA1c, LDL-C, and SBP will be also conducted according to age ( $\leq 60$  and  $> 60$  years), sex (male and female), education levels (junior high school degree or below, high school education or above), employment status (never worked/unemployed, retired and on duty), smoking status (never, former and current), current drinking (yes or no), prevalent obesity (yes or no), prevalent hypertension (yes or no), prevalent hypercholesterolemia (yes or no). A two-sided P value less than 0.05 is considered statistically significant.

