## **7. Ethics Approval**

The proposed trial complies with the Helsinki Declaration (1996 edition) and the relevant regulations of Chinese clinical trials. The study protocol and informed consent form are approved by institutional review boards of the Nanfang Hospital of Southern Medical University before implementation.

All revisions on protocol or informed consent (excluding administrative changes and revisions that have no impact on the participants, implementation of trial, or data) must be submitted to the Ethics Committee for approval prior to the implementation of amendments. Serious adverse events must be reported to the Ethics Committee as required by the ethics committee.

Before enrollment, the informed consent is accessible to the patients. The background, aim, methods and measurements of the trial are introduced thoroughly by the researcher. Individual rights and obligations, possible risks and benefits during the intervention must be explained in detail. Researchers are responsible to answer questions raised by patients accurately in plain language. Patients are allowed to discuss with family members and decide whether to participate in the study. All subjects approve the collection and use of the trial data and are willing to participate the follow-up. Researchers should obtain the permission of the participants to use the collected data if they withdraw. Participants will be required to sign informed consent before enrollment. Informed consent will be kept as original materials for future reference. The study will be registered on the NIH

60 Clinical Trial website before enrollment.

61 **8. Proposed study timeline**

62 The implementation of the trial is expected to take about 2.5 years after registration in the clinicaltrials.gov  
63 the trial, in which MOP development, personnel training, and subject recruitment take about 1 year.  
64 Intervention and data collection take about 1 year, data entry, data analysis and manuscript preparing take about  
65 0.5 years.

66

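### Section 2.3.3 does not separate stopping the messages from stopping follow-up, which undermines the intention-to-treat analysis; its non-compliance clause can act only in the intervention arm

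*Protocol*

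**What the plan says.** Section 2.3.3 of the protocol gives three groups of termination criteria, all worded for subjects in general and not for one arm:

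- "Subjects with serious complications or severe adverse events"
- "Subjects are pregnant or treated with dialysis"
- withdrawal of consent, "unwillingness to compliant to the intervention or other unexpected reasons"

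Section 3.2 defines SAE, under the same term that 2.3.3 uses, to include "a hospitalization for any cause other than routine delivery". Section 3.4 uses the word differently, as a grade: "Severe: disrupting daily activities and intolerable, requiring participants to take medication immediately". It also counts an event as adverse only if its link to the intervention is rated definite or probable.

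Section 2.4 gives usual care to both arms and messages to one. Section 2.6.2 mentions termination visits in its heading, but neither its text nor Table 2 describes any visit or measurement after termination.

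Section 5.2.1 analyses participants by their "randomization assignments, regardless of their subsequent status", and plans multiple imputation by Markov chain Monte Carlo, tied to its multivariable analyses. Section 7 adds: "Researchers should obtain the permission of the participants to use the collected data if they withdraw". The same section says that participants agree at entry to data collection, data use and follow-up.

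**The concern.** The primary outcome is the change from baseline to month 12 in HbA1c, LDL-C and SBP. An analysis that disregards what happens after randomisation needs month-12 values from people who stop the messages, fall ill or lose interest. A rule that ends participation for those same reasons stops the values from being collected.

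The non-compliance clause is the sharper problem. Only the messaging arm has an intervention to be unwilling to comply with. If the clause ends follow-up, it removes the least engaged participants from that arm, while equally disengaged controls stay. The comparison then drifts towards engaged recipients against all controls, probably in favour of the messages. A larger sample does not cure this, and a later statistical analysis plan cannot recover outcomes that were never measured.

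**Working it through.** **Does termination end follow-up?** No section says so outright. Four points lean that way.

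1. The criteria apply to controls, who have no study treatment to stop. For a control, termination on pregnancy, dialysis or an adverse event has meaning only if participation ends.
2. Pregnancy and dialysis echo two exclusion criteria in 2.3.2 (pregnancy and end-stage kidney disease), which govern being in the study.
3. Non-compliance is grouped with withdrawal of consent.
4. Nothing in 2.6.2 or Table 2 provides for measurements after termination.

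**Which criteria are one-sided?** Only unwillingness to comply. Adverse events, pregnancy, dialysis and consent withdrawal can occur in either arm.

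**How large could the bias be?** Section 2.3.3 gives no rate, so this is illustration only.

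Inputs from section 5.1, using its SDs as the SDs of change: HbA1c 0.5/1.6 = 0.3125 SD; SBP 5/18 = 0.278 SD; LDL-C 0.25/0.96 = 0.260 SD. The mean is d = 0.284 SD.

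Let x be the share of the intervention arm terminated for non-compliance (assumed), and g their worse prognosis in SD (assumed). Suppose they lose all benefit, and the analysis rests on those remaining or imputes from them.

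- Estimated effect: d + xg
- As-randomised effect: (1 − x)d
- Bias: x(d + g)

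| x | bias, g = 0 | share of d | bias, g = 0.3 | share of d |
|---|---|---|---|---|
| 5% | 0.014 SD | 5% | 0.029 SD | 10% |
| 10% | 0.028 SD | 10% | 0.058 SD | 21% |
| 15% | 0.043 SD | 15% | 0.088 SD | 31% |

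In HbA1c units with g = 0, the bias is 0.5x: 0.025, 0.05 and 0.075 percentage points. With g = 0.3 it is x(0.3125 + 0.3) × 1.6: 0.05, 0.10 and 0.15 points, or about 10-29% of the planned 0.5.

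**False positives when there is no true effect.** Take 400 × 0.8 = 320 evaluable controls and 320(1 − x) in the intervention arm, one outcome, missingness ignored. The shift is b = xg and se = √(1/320 + 1/(320(1 − x))). The two-sided rejection rate is 1 − Φ(1.96 − b/se) + Φ(−1.96 − b/se). For x = 10% and g = 0.5: b = 0.05, se = 0.0812, rate 9.4%. For g from 0.25 to 0.5 the rate is:

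- x = 5%: 5.3-6.1%
- x = 10%: 6.1-9.4%
- x = 20%: 9.2-22.2%

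**Power.** With 320 per arm, power is 97.7% (HbA1c), 94.0% (SBP) and 90.9% (LDL-C). With a further 20% lost from the intervention arm only, it is 96.1%, 91.2% and 87.4%. The issue is bias, not power.

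The stated 400 per arm does not follow from the single-outcome inputs. At 80% power they give 161, 204 and 232 per arm, or 202, 255 and 290 after dividing by 0.8. That is a separate matter, and this point does not rest on it.

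**The case against.** The strongest reply is that the protocol never says outcome collection stops. Intention-to-treat fixes who is analysed and in which arm, so terminated participants can still be analysed as randomised. Imputation is planned, and interim values (blood pressure at months 1, 2, 3, 6 and 9; HbA1c and lipids at months 3, 6 and 9) could inform it. This stands in part: 2.3.3 undermines 5.2.1, but a flat contradiction is not shown. Imputation is not a full answer. The text does not say whether it covers the primary scaled marginal model. Standard imputation within arm would also fill non-compliers' values from participants still receiving messages, which leaves the xd term in place.

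A reader might also infer more than the document supports:

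- **That outcomes are lost selectively from the intervention arm under all the criteria.** Only the non-compliance clause is one-sided.
- **That every hospitalised participant must be terminated.** Section 3.2 points that way, but the attribution rule and the second use of the word in 3.4 leave the scope unclear. A claim that hospitalisations would use up the 20% dropout allowance needs that reading and a rate the document does not give.
- **That section 7 lets participants vanish from the analysis on termination.** That would need withdrawal and then refusal of permission, and the section already records agreement to data use at entry. The consent pages are not available to settle it.
- **That the bias has a known size.** Both x and g are assumed, and 2.4 sets no compliance threshold from which x could be derived.

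**Conclusion.** The point holds as an unresolved conflict in the protocol's own text. Section 2.3.3 does not distinguish the end of messaging from the end of follow-up. Its natural reading is that outcome collection ends, which undermines the analysis promised in 5.2.1. One clause can act only in the intervention arm.

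The size cannot be fixed from the document. If terminated participants lose all benefit and otherwise share the others' prognosis, one-sided termination of 5-15% overstates the effect by 5-15% of the planned effect. A worse prognosis makes it larger. Partial retained benefit, a better prognosis or continued outcome collection makes it smaller. If follow-up does continue after termination, the bias largely disappears, and stating that is the remedy.

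This is more than a detail to leave to the statistical analysis plan, because it decides which data will exist.

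**What to change.** Reconcile 2.3.3 with 2.6.2, 5.2.1 and 7:

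- State that stopping the messages, or meeting a termination criterion, does not end outcome follow-up.
- State that HbA1c, LDL-C and SBP are still collected at the scheduled visits through month 12, in both arms, unless the participant withdraws consent to follow-up.
- Align the section 7 sentence on permission at withdrawal with the agreement to data use given at entry, so that the status of data already collected is clear.
- Reconcile the term for adverse events in 2.3.3 with 3.2 and 3.4, so that the scope of the first criterion is clear.

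When messages should stop is a matter for the sponsor. The cost is protocol wording, with consent wording if needed, and some continued visits for participants whose visits are already scheduled within the planned 800.
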